## ○ Sample Size

The primary combined endpoint will be cardiac death and HHF at 12 months. As a conservative estimate a combined cardiac death and HHF event rate of 8.5% at 12 months in the conservative arm for all-comer STEMI patients will be used. To demonstrate a 25% reduction in the primary composite endpoint in the RIC-treated group (from 8.5% to 6.4%), with 80% power and at the 5% significance level, 2395 patients per treatment arm are required which equates to 4790 patients in total. Therefore, 5400 STEMI patients will be recruited (allowing for a 10% drop out rate at 12 months) between Denmark and the UK (2600 STEMI patients in Denmark and 2800 STEMI patients in the UK). If the event rate in the control arm is higher than the estimated 8.5% or the losses less than 10% then the power will increase.

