and Kaplan-Meier curves will be produced. The time scale used for survival analysis will be time to the primary endpoint since randomisation. Participants will be censored if they die of a non-cardiac cause, are lost to follow-up, withdraw from the study, or at 12 months after randomisation. The assumptions underlying the Cox model will be assessed and if there is clear non-proportionality hazard ratios will be presented separately for the relevant time periods.

In addition risk differences at one year, again stratified by trial, will also be calculated together with 95% confidence intervals.

- **Analysis of Secondary, and Other Efficacy Endpoints**

- Cardiac death and HHF at 30 days**

The RIC and control arms of the trial year will be compared on rate of the first occurrence of cardiac death or HHF up to 30 days following randomisation. Hazard ratios and 95% confidence intervals will be calculated using Cox proportional hazards modelling, stratified by trial, and Kaplan-Meier curves will be produced. The time scale for analysis will be time since randomisation. Participants will be censored if they die, are lost to follow-up, withdraw from the study, or at 30 days after randomisation. The risk difference stratified by trial together with 95% confidence intervals will also be calculated.

- Individual components of cardiac death and HHF at 30 days and 12 months**

Survival analysis will be used to examine the individual components of the composite outcome, using the same methods as outlined above.

- All cause death, repeat coronary revascularisation, reinfarction, stroke at 30 days and 12 months**

Survival analysis will be used to examine each of these clinical outcomes and MACCE (all-cause death, repeat coronary revascularisation, reinfarction, or stroke) using the same methods as outlined above.

- Repeat HHF and cardiac death**

In order to take account of recurrent HHF in patients while also accounting for the competing mortality, a parametric joint frailty model will be used for

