outcomes up to 12 months adjusted for trial. The aim is to analyse repeat HHFs while accounting for their associated mortality risk by specifying distributions for recurrent HHFs and for time to cardiac mortality, and including individual-specific latent variables to allow for an association between the two event processes. This results in a hazard ratio and 95% CI for recurrent HHF which takes into account mortality as informative censoring as well as a hazard ratio and 95% CI for cardiac death. If there are any problems encountered with model development a negative binomial model will be used.(1-3) Repeat HHFs alone will be analysed using a negative binomial model.

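### Kaplan-Meier with death censored slightly overstates the absolute risk of HHF alone, reinfarction, stroke and revascularisation; cumulative incidence should replace it

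*Supplement*

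**What the plan says.** All references are to SAP version 3 unless stated.

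- **5.3, primary composite.** Cox regression stratified by trial, Kaplan-Meier curves and, in a separate sentence, one-year risk differences stratified by trial. The censoring rule is "Participants will be censored if they die of a non-cardiac cause", alongside loss to follow-up, withdrawal and reaching 12 months.
- **5.4.1, composite at 30 days.** Cox regression again, "and Kaplan-Meier curves will be produced", plus a stratified risk difference. Here the censoring list names death without qualification. Read literally, that would censor cardiac deaths, which are events in this composite.
- **5.4.2, HHF alone and cardiac death alone.** "Survival analysis will be used to examine the individual components of the composite outcome, using the same methods as outlined above".
- **5.4.3.** The same methods for all-cause death, revascularisation, reinfarction, stroke and MACCE.
- **5.4.4, recurrent HHF.** The only place where competing mortality is named. A joint frailty model is built "by specifying distributions for recurrent HHFs and for time to cardiac mortality". Non-cardiac death is not mentioned. The fallback is: "If there are any problems encountered with model development a negative binomial model will be used". The section then plans a negative binomial model for repeat HHFs on their own.

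No cumulative incidence function, Aalen-Johansen estimator or Fine-Gray model appears anywhere, and no estimator is named for the risk differences.

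**The concern.** A patient who has died can no longer be admitted with heart failure, reinfarct, have a stroke or be revascularised. Censoring that patient treats them as still at risk, with the same future hazard as survivors. One minus Kaplan-Meier is therefore never below the cumulative incidence, and it is above it whenever deaths precede events.

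What is at stake is absolute risk. HHF is one of the two components of the primary endpoint, and its 12-month risk by arm is likely to be quoted. The trial's hypothesis is that RIC lowers cardiac death, so the competing event may itself differ between arms. A Kaplan-Meier difference would then miss HHFs that occur because more patients survive to have them. The SAP recognises this for recurrent HHF in 5.4.4 but makes no such provision for first HHF.

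**Working it through.** **The plan's own figure.** The SAP gives no number on this point. Its sample size rests on "a combined cardiac death and HHF event rate of 8.5% at 12 months", a 25% reduction, "with 80% power and at the 5% significance level". With p1 = 0.085, p2 = 0.75 × 0.085 = 0.06375 and a two-sided test:

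n = (1.960 + 0.842)² × (0.085 × 0.915 + 0.06375 × 0.93625) / 0.02125² ≈ 2389 per arm, or 2393 with the pooled-variance form, against the stated 2395. The sample size is sound, so the issue is only the estimator.

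**Formulas.** Let F1 be the true 12-month cumulative incidence of the non-fatal event and F2 that of death before it. With constant hazards (assumed):

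- total hazard L = −ln(1 − F1 − F2)
- event hazard h1 = L × F1 / (F1 + F2)
- one minus Kaplan-Meier = 1 − exp(−h1)
- upper bound, if every death precedes every event: F1 / (1 − F2)

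**A. Rates compatible with the planned 8.5%.** HHF of 4% to 8% is assumed. Cardiac death without prior HHF is then 8.5% minus the HHF rate. Non-cardiac death is assumed to be 0.5% to 2%.

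Example: HHF 5%, non-cardiac death 0.5%, so F2 = 3.5% + 0.5% = 4%.
L = −ln(0.91) = 0.0943; h1 = 0.0943 × 5/9 = 0.0524; 1 − exp(−0.0524) = 5.10%. The overstatement is 0.10 points, or 2.1% relative.

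| HHF | Non-cardiac death | F2 | 1 − KM | Excess, points | Relative | Excess at upper bound |
|---|---|---|---|---|---|---|
| 4% | 2% | 6.5% | 4.14% | 0.14 | 3.5% | 0.28 |
| 5% | 0.5% | 4.0% | 5.10% | 0.10 | 2.1% | 0.21 |
| 5% | 2% | 5.5% | 5.15% | 0.15 | 2.9% | 0.29 |
| 6% | 1% | 3.5% | 6.11% | 0.11 | 1.8% | 0.22 |
| 8% | 0.5% | 1.0% | 8.04% | 0.04 | 0.5% | 0.08 |

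**B. Mortality cited in ERIC-PPCI protocol version 5, section 30.1.** That section quotes 8.7% (UK registry) and 9.4% (Danish study) total one-year mortality, and 8% readmission with heart failure.

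- HHF 8%, death 8.7%: L = −ln(0.833) = 0.1827; h1 = 0.1827 × 0.08/0.167 = 0.0875; 1 − exp(−0.0875) = 8.38%. Excess 0.38 points, about 5% relative; upper bound 8.76%.
- HHF 8%, death 9.4%: 8.41%, excess 0.41 points; upper bound 8.83%.

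**C. Rarer outcomes.** For an assumed 2% to 3% event such as stroke or reinfarction, with death of 3% to 9.4%, the excess is 0.03 to 0.15 points.

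**D. Primary composite.** Only non-cardiac death competes. With F1 = 8.5% and F2 of 0.5% to 2% (assumed), the same formulas give an excess of 0.02 to 0.09 points.

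**E. Risk differences, if read from the curves.** With both hazards cut by 25% in the RIC arm (assumed), the Kaplan-Meier HHF difference is too large by 0.02 to 0.06 points under A. Under B (8% HHF, 8.7% death) it reads 2.03 instead of 1.87 points. If RIC cut only death, Kaplan-Meier shows zero where the true HHF risk is higher with RIC by 0.01 to 0.04 points under A and about 0.1 under B. For scale, 1.96 × √[(p1q1 + p2q2)/2395] gives a 95% half-width of 1.04 to 1.45 points across A.

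**The case against.** The strongest reply is that nothing comparative changes. The SAP's stated comparison is the Cox hazard ratio, and censoring competing deaths leaves it valid as a cause-specific hazard ratio. Any error in a risk difference is well inside its confidence interval. That stands, and it limits the point to the reported absolute risks.

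Four stronger inferences are tempting, and the documents do not support them.

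- **That the risk differences are biased.** No estimator is named. Stratified proportions of all randomised patients would be free of this particular error, although they would count patients lost or withdrawn as event-free, and the plan allows for 10% drop-out. The bias is conditional on using the curves.
- **That the error is typically 5% or more.** An HHF risk of 8% inside an 8.5% composite leaves only 0.5% for cardiac death without prior HHF, so 8.7% mortality would have to be almost all non-cardiac or to follow an HHF. The cited figures are also total mortality, and the protocol says that it planned on lower rates than the published ones.
- **That no HHF analysis would account for death if the joint model failed.** The composites count cardiac death as an event alongside HHF. They do not isolate HHF.
- **That the fallback in 5.4.4 simply ignores death.** It sits under a heading covering repeat HHF and cardiac death, and a separate negative binomial model is planned for repeat HHFs alone. It could mean a count of both. The wording leaves this open.

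It is also fair to say that the 12-month rule names only non-cardiac death and is written for the composite. Censoring at cardiac death for HHF alone is implied by the reference to the same methods. The SAP offers no other handling.

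**Conclusion.** The point holds as a small correction to absolute risks. The Kaplan-Meier curves planned in 5.4.2 and 5.4.3 for HHF alone, reinfarction, stroke and revascularisation will overstate risk. For HHF the excess is roughly 2% relative (0.04 to 0.15 points) at rates that fit the plan, and about 5% relative at the cited mortality. The direction needs no assumption. The size rests on constant hazards, an assumed split of the 8.5% composite and assumed non-cardiac mortality; if all deaths came first it would about double.

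The cause-specific hazard ratios, the primary conclusion and the sample size are unaffected. All-cause death and MACCE are also unaffected, because every death is an event in both. In 5.4.4 the gaps are that non-cardiac death has no stated place in the joint model, and that the fallback may reduce to the model already planned for repeat HHFs alone.

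**What to change.** 1. Keep the Cox models in 5.3 to 5.4.3. Label the hazard ratios cause-specific wherever a competing death is censored.
2. For HHF alone, reinfarction, stroke and revascularisation, replace Kaplan-Meier by Aalen-Johansen cumulative incidence with all-cause death as the competing event. For cardiac death alone, and for the composite where absolute risk is shown, the competing event is non-cardiac death. Keep Kaplan-Meier for all-cause death and MACCE.
3. State the risk-difference estimator: 30-day and 12-month differences from these estimates, stratified by trial.
4. Write the censoring rule separately for each endpoint, so that the 30-day composite does not appear to censor cardiac deaths.
5. In 5.4.4 include non-cardiac death in the terminal process, and name a fallback that retains death, for example total HHFs plus cardiac deaths.

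The cost is SAP wording, one standard routine and a little more analysis work. Deaths are already collected and adjudicated. Reported risks for the non-fatal outcomes will be slightly lower.

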### Implantable cardioverter-defibrillators (ICD), biventricular pacemakers (BiV) and single/dual chamber pacemakers at 12 months

The proportions with an implantable cardioverter-defibrillator (ICD), biventricular pacemaker (BiV) or single/dual chamber pacemaker at 12 months will be compared using a generalised linear model. A risk ratio and corresponding 95% confidence interval will be calculated.

#### ○ Subgroup analysis

A limited number of pre-specified subgroup analyses are planned on the primary outcome. These will be limited to age, diabetic status, LAD vs non-LAD STEMI, TIMI flow (0-1 and 2-3) pre-angioplasty and time of first medical contact to PPCI (i.e. balloon time). The subgroups will be analysed by inclusion of an interaction term between treatment group and the subgroup in the Cox regression model.

#### ○ Cardiac Biomarkers Substudy

Values of high-sensitivity troponin T will be converted into a 48 hour area under the curve (AUC) summary measure for analysis. Differences in the mean AUC together with 95% confidence intervals will be calculated using a linear regression model. Troponin T will be collected at admission and 6-8, 24, and 48-72 hours post-PPCI in CONDI-2, and at admission and 6, 12, 24 and 48 hours post-PPCI in ERIC-PPCI. Where necessary, multiple imputation by chained equations will be used to account for missing information. Separate imputation models will be used for each trial. In CONDI-2, the troponin T measurement at 48-72 hours post-PPCI will be split in to those occurring at 48 hours (between 36 and 60 hours after the admission measurement) and those occurring at 72 hours (between 60 and 84 hours after the admission measurement) before multiple

imputation on all measurements up to 72 hours post-PPCI is performed. In ERIC-PPCI, multiple imputation on all measurements up to 48 hours post-PPCI will be performed. Twenty imputed datasets will be generated separately for each trial before being combined. The estimated difference in mean 48 hour AUC between the two treatment groups will be calculated using Rubin's rules. The distribution of the outcome variable will be investigated for non-normality and if necessary a data transformation will be made or a non-parametric statistical analysis will be conducted.

The following variables will be included in the multiple imputation models: troponin-T at each time point; treatment group; country (CONDI-2 only); gender; baseline age, diabetes, hypertension, systolic blood pressure, Killip class, and body weight; use of aspirin,  $\beta$ -blockers, nitrates, diuretics, Clopidogrel, Ticagrelor/Brillique, and metformin at admission for PPCI; previous myocardial infarction; peripheral vascular disease and hypercholesterolaemia at admission for PPCI; call to balloon time; pre/peri-procedural use of nitrates; length of index hospitalisation; and cardiac death within 12 months.

CK-MB will be analysed using data from the CONDI-2 trial only. Values of CK-MB will be converted into a 48 hour AUC summary measure for analysis. Where necessary, multiple imputation by chained equations will be used to account for missing information (as described for troponin T). The estimated difference in mean 48 hour AUC between the two treatment groups will be calculated using Rubin's rules. The distribution of the outcome variable will be investigated for non-normality and if necessary a data transformation will be made or a non-parametric statistical analysis will be conducted.

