## 33. Randomisation

### 33.1. Randomisation procedure

Patients will be randomised to either RIC or sham RIC by a designated research investigator, this investigator will therefore be unblinded to treatment allocation. Randomisation will be coordinated centrally by the LSHTM CTU via a secure website [www.sealedenvelope.com](http://www.sealedenvelope.com) and will be stratified by centre using random permuted blocks.

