### **37.1. Procedure**

From each patient, a single blood sample will be taken at each of the 5 timepoints (0, 6, 12, 24 and 48 hours following PPCI procedure). Each blood sample will be analysed at the local hospital.

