### **41.2. Statistical analysis**

A detailed statistical analysis plan will be produced prior to unblinding of any data. The primary analysis will be a comparison of the cardiac death or HHF event rate one year after randomisation between the RIC and sham RIC arms of the trial amongst all STEMI patients. Hazard ratios and confidence intervals will be calculated using Cox proportional hazards modelling and Kaplan-Meier curves will be produced. In addition risk differences at one year will also be calculated together with 95% confidence intervals. The results for the individual components of the primary endpoint will also be presented together with other time to event secondary endpoints such as cardiac death or HHF at 30 days. Differences in means (continuous variables) together with 95% confidence intervals will be calculated using linear regression models and analysis of covariance techniques where appropriate. The primary analysis will be performed on an intention to treat basis i.e. by including all patients where possible according to the group to which they were randomised irrespective of whether they received the intervention as allocated. A secondary per protocol analysis will be undertaken including only patients who receive the allocated intervention as intended.

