- Quality of life at 6-8 weeks and 12 months (EuroQol EQ-5D-5L)

All these outcomes are relevant to STEMI patients and have the potential to change clinical practice.

- **Endpoints**

An independent end-point committee will adjudicate primary and secondary clinical endpoints.

- **Primary clinical endpoint**

- Cardiac mortality and HHF at one year

- **Secondary clinical endpoints**

- Myocardial infarct size at day three (72 hour area under curve serum creatinine kinase). Furthermore, TnT in a subset of patients (Aarhus, Aalborg, Belgrade)
- Left ventricular function on day three and three months post pPCI (Echocardiography)
- Myocardial re-infarction/recurrent, stroke and revascularisation at one year
- Persisting ST-segment elevation on ECG 90 min. after primary PCI

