**Summary of Changes in the CONDI-2 protocol**

Proximal LAD STEMI: Patients presenting with the larger proximal LAD STEMI have worse clinical endpoints. In the AMISTAD II study (2,118 patients), which investigated the effect of adenosine as an adjunct to pPCI, only recruited LAD STEMI patients, and in these patients the 6-month primary combined endpoint was 19.6% (11.3% cardiac death, 8.3% HHF) (18). As a conservative estimate we will use a combined cardiac death and HHF event rate of 15% at 12 months for proximal LAD STEMI patients. To demonstrate a 30% reduction in the primary composite endpoint in the RIC-treated group (from 15.0% to 10.5%), with 80% power and at the 5% significance level, would require 862 patients per treatment arm which equates to 1,724 patients in total (862 proximal LAD STEMI patients each in the UK and Denmark). Therefore, assuming that about 45-50% of all STEMI patients present with a proximal LAD STEMI, in order to recruit 1,724 proximal LAD STEMI patients, we will need to recruit about 4,300 all STEMI patients (allowing for a 5% drop-out rate at 12 months) between UK, Serbia, Spain, and Denmark.

- **Interim analyses**

We will perform an interim analysis for evaluation of the actual event rate after inclusion of 50% of the patients. If this shows lower event rate than expected, a new sample size calculation will be performed. Furthermore, we will perform an independent safety analysis after inclusion of 50% of the patients.

- **Pre-specified subgroup analyses**

We will undertake a limited number of subgroup analyses: age, gender, diabetes, duration from symptom onset to pPCI, and duration from end of RIC to pPCI. These subgroups will be analysed using interaction tests. These factors may influence the response to cardio-protective strategies such as RIC and pharmacological agents.

- **Statistical analysis**

We will produce a detailed statistical analysis plan prior to un-blinding of any data. The primary analysis will be a comparison of the event rate one year after STEMI between RIC and control arms of the trial. We will use survival analyses for cardiac mortality, HHF, and other clinical endpoints. Further, we will use area under the curve to assess the MI size. All patients will be included in the data analysis after the intention-to-treat principle.

- **Project timetables and recruitment feasibility**

The total duration of the study will be 56 months:

- 1) 0-6 months: Study preparation

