## ● ANALYSIS POPULATIONS

### ○ Definition of Populations for Analysis

The primary analysis will be performed on an intention to treat basis, by including all patients where possible according to the group to which they were randomised irrespective of whether they received the intervention as allocated. A secondary per protocol analysis will be undertaken including only patients who receive the allocated intervention as intended.

- Intent-to-treat (ITT)

The intent-to-treat analysis population will include all patients randomised to CONDI-2 and ERIC-PPCI regardless of whether they received their randomised intervention as specified (i.e. including all patients whether or not all cycles of RIC or sham RIC were fully completed according to protocol and whether or not the patient received PPCI).

- Per Protocol (PP)

The per protocol analysis population will include confirmed STEMI patients randomised to CONDI-2 and ERIC-PPCI who received their randomised intervention as specified (i.e. including patients where all four cycles of RIC or sham RIC were fully completed according to protocol and the patient received PPCI).

- STATISTICAL ANALYSIS

- General

The final combined statistical analysis will be performed as pre-specified in this SAP. Any, additional, post-hoc, exploratory analyses completed to support these planned analyses which are presented in the trial reports but not included in this SAP, will be clearly identified as such. Analyses will be stratified by trial (i.e. CONDI-2 or ERIC-PPCI) where indicated below.

- Methods for Handling Missing Data

For the outcomes considered in this analysis, missing data are expected to be minimal. However, multiple imputation methods may be used depending on the scale and pattern of the missing data.

- Analysis of Primary Endpoint – cardiac death and hospitalisation for heart failure 12 months after randomisation.

The primary combined endpoint is defined as the first occurrence of HHF or cardiac death within 12 months of randomisation. The primary analysis will be a comparison of the rate of the first occurrence of cardiac death or HHF between the RIC and control arms of the trial. Hazard ratios and 95% confidence intervals will be calculated using Cox proportional hazards modelling, stratified by trial,

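### The model for the pooled troponin T AUC names no stratum or covariate, so trial, centre and infarct territory are left out and the interval is likely to be wider than it need be.

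*Supplement*

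**What the plan says.** SAP version 3 section 5.6 pools troponin T from the two trials, converts it to a 48-hour AUC, and states: "Differences in the mean AUC together with 95% confidence intervals will be calculated using a linear regression model". No covariate, centre term or trial term is named. The long list of variables in that section belongs to the imputation models. It has country for CONDI-2 only, and neither centre nor infarct territory.

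Elsewhere the documents say:

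- **Trial.** The general rule in SAP 5.1 is "Analyses will be stratified by trial (i.e. CONDI-2 or ERIC-PPCI) where indicated below". The indication is given for the Cox models and risk differences in 5.3 and 5.4.1, and the joint frailty model in 5.4.4 is adjusted for trial. Section 5.6 gives none.
- **Centre.** ERIC-PPCI version 5 section 33.1 says randomisation "will be stratified by centre using random permuted blocks". CONDI-2 version 10 also uses blocked lists stratified by centre.
- **Laboratory.** ERIC-PPCI section 37.1: "Each blood sample will be analysed at the local hospital". Section 37.2 names one platform. CONDI-2 version 10 measures troponin T at some sites only ("Furthermore, TnT in a subset of patients (Aarhus, Aalborg, Belgrade") and does not say where the assay is run.
- **Territory.** SAP 5.5 lists "LAD vs non-LAD STEMI" as a subgroup factor for the primary outcome. The CONDI-2 power section says: "Patients presenting with the larger proximal LAD STEMI have worse clinical endpoints".
- **Model family.** ERIC-PPCI section 41.2 says differences in means "will be calculated using linear regression models and analysis of covariance techniques where appropriate", without naming covariates.

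**The concern.** When randomisation is stratified and the outcome differs between strata, an analysis that leaves the strata out puts between-stratum variation into the error term. The estimate is still unbiased, but its standard error is overstated. A strong baseline predictor that is left out also costs precision: chance imbalance in it adds real variance to the estimate.

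Both apply here. Centre is the stratum in each trial. It also carries the trial, with its different sampling schedule, and any local laboratory difference. The CONDI-2 protocol itself treats proximal LAD infarcts as larger, and AUC is meant to measure infarct size. ERIC-PPCI section 30.2 calls this outcome a major secondary endpoint, so the width of its interval matters.

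The imputation models have the same gap. An analysis adjusted for centre and territory needs both in the imputation models. As written, country separates Belgrade from the two Danish troponin sites but does not separate Aarhus from Aalborg, and ERIC-PPCI has no site-level term.

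**Working it through.** **Inputs from ERIC-PPCI version 5 section 30.2:** control mean 24.6 and SD 20.6 (×10⁴), planned reduction 25%, 80% power, 5% level, 177 per group, 354 in total, 400 after 10% dropout. **Assumed:** a two-sided test (the section does not state it), and R², the share of AUC variance explained by the added terms, taken as 0.05 to 0.30 because the documents give no value.

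**1. The plan's own figure.** Difference = 0.25 × 24.6 = 6.15. Per group, n = 2(1.96 + 0.84)² × 20.6² / 6.15² = 176.1 with unrounded normal quantiles, so 177 per group and 354 in total. 354 / 0.9 = 393.3, so 394, against 400 stated. The figure reproduces with no adjustment.

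**2. Effect of adjustment.** The residual SD becomes 20.6 × √(1 − R²). The 95% half-width at 177 per group is 1.96 × SD × √(2/177).

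| R² (assumed) | Half-width (×10⁴) | Narrower by | n per group for 80% power | Power at 177 |
|---|---|---|---|---|
| 0 | 4.29 | – | 177 | 80.2% |
| 0.05 | 4.18 | 2.5% | 168 | 82.2% |
| 0.10 | 4.07 | 5.1% | 159 | 84.1% |
| 0.20 | 3.84 | 10.6% | 141 | 88.1% |
| 0.30 | 3.59 | 16.3% | 124 | 91.9% |

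**3. Omitted balanced strata.** If balanced centre strata explain a share R² and are left out, the true level of the nominal 5% test is 2[1 − Φ(1.96/√(1 − R²))]. This is 4.4% at R² = 0.05 and 2.8% at 0.20, so the test is conservative, not invalid.

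**4. Territory alone, as an illustration.** Take a 45–50% share (CONDI-2 version 10 gives this for proximal LAD) and assume a ratio of mean AUC, LAD to non-LAD. Then R² = p(1 − p)(m₁ − m₀)²/20.6², with the overall mean held at 24.6. For p = 0.5 and ratio 1.5, m₀ = 19.68 and m₁ = 29.52, so R² = 0.25 × 9.84²/424.36 = 0.057. Over both shares, a ratio of 1.25 gives about 0.02, 1.5 about 0.06, and 2.0 about 0.16–0.17.

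**5. Log scale, which the protocol anticipates.** Assuming a lognormal shape with the same coefficient of variation, the log SD is √ln(1 + (20.6/24.6)²) = 0.729. The planned effect is −ln 0.75 = 0.288. At 177 per group the standard error is 0.729 × √(2/177) = 0.0775, and power is Φ(0.288/0.0775 − 1.96) = 96.0%. At 200 per group the standard error is 0.0729 and power is 97.7%, rising to 98.2% at R² = 0.05 and 99.7% at 0.30. The half-width on the log scale at 177 per group is 1.96 × 0.0775 = 0.152. It falls to 0.148 and 0.127 at the two ends of the R² range, the same proportions as in step 2.

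The pooled number of troponin patients is not given. It exceeds ERIC-PPCI's share, so these power figures are if anything low for the pooled analysis.

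**The case against.** The best defence is that section 5.6 is silent, not restrictive. It does not say that treatment is the only term, and ERIC-PPCI section 41.2 allows analysis of covariance where appropriate. The SAP also refers to separate plans for each trial, which are not shown here. That part stands: a treatment-only model is an inference from silence. But section 41.2 names no covariates, and under the SAP's own rule trial enters only where indicated, which 5.6 does not do. Followed as written, the comparison contains none of these terms.

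A reader might go further and infer that a real infarct-size effect would be missed. The documents do not support this. At the planned 25% reduction on the log scale, power is already about 96% to 98% without adjustment. A materially larger gain needs a smaller effect than the one planned, and the documents give none.

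A reader might also infer that the assays are incompatible across sites. Local assay is documented for ERIC-PPCI only, on one named platform. CONDI-2 says only that samples are analysed immediately, and its shorthand for troponin T is no evidence of a different assay. Laboratory differences would in any case be taken up by a centre term, so the two gains overlap and must not be added.

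Finally, covariate choice in a secondary substudy can be called a matter of preference. That is fair for a long covariate list. It is less fair for the randomisation stratum and one strong predictor already in hand.

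**Conclusion.** The point holds as one of precision and pre-specification. Section 5.6 names no model terms. It leaves out trial, which the SAP handles in its other pooled Cox and frailty analyses, and centre and infarct territory, which are available. Nothing here biases the estimate or upsets the sample size.

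The documents support the direction of the loss, not its size. For an assumed R² of 0.05 to 0.30, the 95% interval would be about 2.5% to 16% narrower with adjustment. If the terms explain almost nothing, the gain vanishes and the centre terms cost a little. The 45–50% share used for territory is stated for proximal LAD, and the LAD to non-LAD ratio is an assumption, so step 4 is illustrative only.

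**What to change.** In SAP 5.6, state that log 48-hour AUC is regressed on treatment, centre (fixed effect) and infarct territory in three categories: LAD, non-LAD, and no culprit or no PPCI. The third category is needed because the intention-to-treat set keeps patients who did not receive PPCI. Centres are nested in trials, so the centre term also absorbs trial and local laboratory. Territory is seen after randomisation, but the cuff cannot change it.

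Add centre and infarct territory to both imputation models so that they match the analysis model.

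Do not restrict the pool to centres reporting a high-sensitivity assay. No document shows a centre using another, and the restriction could discard patients. If one did, a sensitivity analysis is enough.

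The cost is a few words, with no new data collection. The centre terms use some degrees of freedom: ERIC-PPCI plans 30 sites in all, so at most 29 there, and fewer because the substudy runs at selected sites. Centres with few substudy patients may need to be pooled, by a rule written down before unblinding.
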